### Economic evaluation

In order to compare the two therapeutic programmes, a cost-effectiveness analysis will be performed. Direct costs will be calculated by adding the costs of the medication, the use of health-related services and the use of pharmaceutical-related services. According to the International Vademecum (Red Book) 2007–2009, the cost of medications will be calculated by determining the price per milligram during the study, including value-added tax, and multiplying it by the daily dose in milligrams and the number of days receiving such treatment. Costs derived from the use of health related services will be calculated considering OBLIKUE unitary cost database [41]. Costs of pharmaceutical related services will be calculated by multiplying the price of an hour of pharmacist attention by the time spent attending patient concerns and needs.

Indirect costs will be calculated considering the days on sick leave and multiplying them by the minimum daily wage in Spain. Finally, total costs will be calculated by adding direct and indirect costs.

Adherence to pharmacological treatment will be used to compare the benefits of each intervention. To determine which of the interventions is best for maximizing benefits, the incremental cost-effectiveness ratio (ICER) will be calculated. The ICER expresses the relation between the costs and effects of one intervention compared with another [42]. To address uncertainty in the ICER sampling distribution, non-parametric bootstrapping will be carried out [43]. Five thousand replications will be carried out for each treatment comparison.

As the duration of the study was only 6 months, neither costs nor outcomes were subject to discounting [42].

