### Setting

Gavà is a city situated in the province of Barcelona (Catalonia, Spain) approximately 15 kilometres south of Barcelona city. With a total area of 30.9 square kilometres and a population of more than 45,000 inhabitants, the city has two primary care health centres (PCHCs) (Gavà-1 and Gavà-Doctor Bartomeu Fabrés Anglada) that provide medical care to the whole population of Gavà. Patients will be recruited at those PCHCs from October 2008 to October 2009. 23 general practitioners (GPs) from the PCHCs voluntarily participate in the study and deal with the identification and subsequent recruitment of the patients.

Altogether there are 14 community pharmacies in Gavà that were asked to participate in the study. In addition, there is a community pharmacy in the adjacent town of Viladecans located very near to one of the PCHCs that was also asked to participate. Two of the pharmacies (13%) refused to participate, one citing heavy workload and the other a lack of interest in the study. Finally, 13 pharmacies with a total of 34 pharmacists will be responsible for providing patients with the intervention and usual care during the 6 month follow-up period.

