### Intervention and usual care

Patients in the intervention group will receive the support programme in community pharmacy (PRODEFAR) every time they go to the pharmacy to pick up the medication or to ask for counselling in the course of the 6 months of the study. Pharmacists participating in the study received 8 hours of training about PRODEFAR prior to the study. The training followed a manual created for the study and is accredited by the Catalonian council of continuous pharmaceutical training (*Consell Català de la formació farmacèutica contínua*) (Reference Number: 09F00676).

PRODEFAR consists of a series of educational interventions focused on improving patients' knowledge of antidepressant medication, as well as making patients aware of the importance of compliance to the medication. Moreover, in patients with a sceptical attitude towards the medication, the intervention will aim to reduce stigma, reassure the patient about possible side-effects, and stress the importance of carrying out GPs' advice. First contact in the PRODEFAR is expected to take between 20 and 30 minutes, subsequent interventions are expected to take between 10 and 15 minutes.

Regardless of whether participants belong to the intervention group or not, they receive the usual pharmaceutical care as well as the treatment considered most appropriate by their physician. Patients receiving usual care get ordinary advice about medication when collecting it. Any concerns and questions addressed to the pharmacist are also answered.

Patients in the intervention group are asked to avoid conversations concerning the PRODEFAR with patients from the control group. The importance of this requirement is emphasised to patients from both groups at baseline assessment.

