### Economic evaluation

Client Service Receipt Inventory (CSRI) [40] is a questionnaire for collecting information about use of healthcare and social care services as well as other economic impacts. In our study, we adapted it to take into account the costs due to lost production as well as the cost of medicines, the costs of healthcare use and social care services, and the costs for patient in terms of travelling expenses and time lost. Patients are asked to give details of services and medicines that they have used during the previous 3 months due to depression or for other reasons. Services included hospital care, primary healthcare and social care, as well as the provision of aids, tests and medication. The length of stay is recorded for inpatient episodes, whilst the number of contacts with other services is recorded.

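### The total-cost sum has no term for patient travel, patient time or programme training and does not name social care, so it fits neither a health-system nor a societal perspective

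*Protocol article*

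**What the plan says.** Two sections of the protocol article carry the title Economic evaluation.

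The one under Measurements describes the instrument. The CSRI was adapted to take account of lost production, medicines, "the costs of healthcare use and social care services, and the costs for patient in terms of travelling expenses and time lost". Table 2 schedules it at baseline, 3 months and 6 months as the source of direct and indirect costs.

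The one under Statistic analysis describes what is summed:

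- Direct costs: "Direct costs will be calculated by adding the costs of the medication, the use of health-related services and the use of pharmaceutical-related services".
- Pharmacy services are valued by "multiplying the price of an hour of pharmacist attention by the time spent attending patient concerns and needs".
- Indirect costs: "Indirect costs will be calculated considering the days on sick leave and multiplying them by the minimum daily wage in Spain".
- Total: "total costs will be calculated by adding direct and indirect costs".

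Intervention and usual care adds that "Pharmacists participating in the study received 8 hours of training about PRODEFAR prior to the study". Setting gives the number trained and delivering care: "13 pharmacies with a total of 34 pharmacists". No costing perspective is stated in either section.

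**The concern.** The analysis section names each component of total cost and how it is valued, then adds them. Items the trial sets out to collect have no place in that sum, and no reason is given for leaving them out. An analyst who follows the text would drop patient travel and patient time from the ICER, and probably social care too.

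The sum also has no term for training pharmacists to deliver the programme. Training exists only because of the programme, and the longer pharmacy contacts occur in the intervention arm. Leaving out training and the extra patient time therefore lowers the incremental cost. The planned bootstrap resamples the same incomplete costs, so it cannot show or repair this.

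Cost-effectiveness is a stated aim, and the Discussion says the programme would be recommended for usual care if proven effective and cost-effective. What the cost side contains therefore matters to the reader the trial is meant to inform.

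**Working it through.** **Step 1. Items collected against items summed.**

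| Item | Collected (Measurements, Economic evaluation) | In the sum (Statistic analysis, Economic evaluation) |
|---|---|---|
| Medicines | yes | yes |
| Healthcare use | yes | yes |
| Social care | yes, named apart from healthcare | not named |
| Patient travel | yes | no term |
| Patient time lost | yes | no term |
| Lost production | yes | yes, as sick leave |
| Pharmacist contact time | not named | yes |
| Programme training | not named; 8 h per pharmacist stated elsewhere | no term |

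**Step 2. Perspective.** A health-system total would exclude sick leave, but sick leave is in. A societal total would include patient time and travel, but both are out. The sum as written is neither.

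**Step 3. Size of the training omission.** The plan gives no price, total cost or ICER, so there is no figure of its own to reproduce and the comparison can only be made in hours.

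Inputs:

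- 34 pharmacists (Setting).
- 8 h of training each (Intervention and usual care).
- 194 patients (Sample size) allocated 1:1 (Enrolment, randomization and allocation), so 194 / 2 = 97 intervention patients.
- First contact 20-30 min, later contacts 10-15 min (Intervention and usual care).
- Number of contacts per patient: not stated. Assumed here to be v = 1, 3 or 6.

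Training hours: 34 x 8 = 272.

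Per intervention patient, if all is charged to the trial: 272 / 97 = 2.80 h.

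Contact time per patient: from 20 + (v - 1) x 10 min to 30 + (v - 1) x 15 min.

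| Contacts (assumed) | Contact time | In hours | Training / contact time |
|---|---|---|---|
| 1 | 20-30 min | 0.33-0.50 | 5.6-8.4 |
| 3 | 40-60 min | 0.67-1.00 | 2.8-4.2 |
| 6 | 70-105 min | 1.17-1.75 | 1.6-2.4 |

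**Step 4. Effect of spreading the training.** The 2.80 h is an upper figure, because trained pharmacists could treat later patients. Over four times as many patients (388) it is 272 / 388 = 0.70 h. At six contacts the ratio is then 0.70 / 1.75 = 0.4 to 0.70 / 1.17 = 0.6. Also at six contacts, training equals contact time when spread over 272 / 1.75 = 155 to 272 / 1.17 = about 233 patients.

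**Step 5. Patient time.** Patients spend the same contact minutes as pharmacists: 20-30 min at one contact and 70-105 min at six. These are gross figures. Control patients also receive advice and have their questions answered, for a time the article does not give. Only the difference between arms enters the ICER, so the incremental patient time is smaller than this by an unknown amount.

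**The case against.** The strongest reply has four parts.

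- *Collecting more than is summed is not a contradiction.* One section describes an instrument and the other a valuation. That is fair as far as the word goes. But the first says the instrument was adapted in order to take these costs into account, and the second then lists its terms one by one. It is an unexplained narrowing in what is written, not a detail lost in condensing.
- *Health-related services may be a short label that includes social care.* This is possible, since the instrument's services are listed together at one point. The same paragraph also names healthcare and social care separately, so the text is ambiguous. Travel and patient time remain outside on any reading.
- *Training is a one-off set-up cost, and whether to count it is a convention.* No sentence promises to cost it, so its absence is not an inconsistency. How to spread it is a judgement, which is why it belongs in a sensitivity analysis. Costing it at zero still sits badly with an intention to recommend wider implementation, where further pharmacists would need training.
- *The programme needs no extra journeys.* It is given when patients collect medication or seek counselling, so extra travel is not established. If the programme works, social care use and travel could fall, and leaving them out would then count against it.

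A reader might infer that all the omissions together make the programme look cheaper than it is, and that the ICER and its interval are biased in its favour. The documents do not support that. The sign is clear only for training and for extra patient time in programme contacts, and the net sign over all omitted items is not established.

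**Conclusion.** The point holds with a limited claim about bias. The total-cost sum has no term for patient travel or patient time although both are collected, does not name social care, and values training at zero. It fits neither a health-system nor a societal perspective.

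Leaving out training and extra contact time for patients understates the intervention's incremental cost. For social care and travel the direction is unknown. The net change in the ICER cannot be computed because no prices are given, and hours alone do not show how the omitted items compare with medication, health services and sick leave.

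The training figure of about 2.8 h per intervention patient is a ceiling. It assumes that all 34 pharmacists took the full 8 h and that the whole cost falls on 97 patients. On that basis it exceeds the costed contact time at each contact number tried (1, 3 and 6), but it need not once the cost is spread over later patients. The change is worth making because it alters what enters the ICER and uses information the trial will already have.

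**What to change.** In the Economic evaluation section under Statistic analysis:

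1. State the costing perspective.
2. Add social care, patient travel and patient time from the adapted CSRI to the total, and label that total societal. If the CSRI answers do not capture time spent in programme contacts, the contact time already needed to cost pharmacist attention can supply it for both arms.
3. Include the 272 training hours as an intervention-arm cost in a sensitivity analysis, once charged wholly to the trial and once spread over a stated larger number of patients.

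The cost is a change of wording, slightly more costing work and a possibly less favourable ICER. No new data collection is needed.

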**Economic evaluation**				

Direct and indirect costs	CSRI – adapted	X	X	X

T0 = Baseline, T1 = 3 months after baseline, T2 = 6 months after baseline.

SCID-I: Structured Clinical Interview Axis I DSM-IV; MAQ: Medication Adherence questionnaire; PHQ-9: Patient Health Questionnaire 9-item depression module; EuroQOL-5D: European Quality of Life Scale – 5 domains; STAI-S: State-Trait Anxiety Inventory (State subscale); CSRI: Client Service Receipt Inventory.

Clinical diagnosis is made using the research version of the Structured Clinical Interview for DSM-IV Axis I Disorders (SCID-I) [24,25]. Patients are interviewed in the modules of major depression (present and past), dysthymic disorder, anxiety disorder and adjustment disorder as defined according to DSM-IV criteria. Due to the pragmatic character of the study, GPs are blind to the DSM-IV diagnosis and patient inclusion and follow-up is performed according to their usual practice.

The primary outcome measure of our study is adherence to prescribed antidepressant medications, which is assessed through two methods:

1) pharmacy records: every time a patient buys their medication, the pharmacist registers the date of prescription, the date of dispensation and the number of pills dispensed. At 3 and 6 months from baseline, the patient is asked to present the stock of antidepressant medication and any surplus antidepressants following a GP recommended change in medication. To minimize bias, the patient is not told that the aim is to assess compliance. The pharmacist registers the stock of every medication and the percentage of medication intake is calculated by formula: (Number of doses removed/Number of doses prescribed)*100. Poor adherence is defined as taking less than 80% of the prescribed doses. There are two disadvantages of measuring adherence this way: the patient can remove pills but not take them, and this formula does provide information about the timing of the dose removal.

2) self-reported: adherence to prescribed antidepressant medications is assessed with the 4-item scale developed by Morisky et al [26]. The scale asks patients to respond "yes" or "no" to a set of 4 questions. A positive response to any question indicates a problem with adherence. Patients who respond "yes" to any of the items are categorized as non-adherent.

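### The drug-cost rule has no term for quantity dispensed; if its daily dose is the prescribed dose, it misses antidepressant doses never bought during treatment, although the ICER's effect counts them

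*Protocol article*

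**What the plan says.** In the protocol article, the Economic evaluation section under Statistic analysis fixes the cost of medication by "determining the price per milligram during the study, including value-added tax", and then "multiplying it by the daily dose in milligrams and the number of days receiving such treatment". The result enters the ICER numerator: "Direct costs will be calculated by adding the costs of the medication, the use of health-related services and the use of pharmaceutical-related services". Sick-leave costs are then added to give total cost. For the other side of the ratio the section states: "Adherence to pharmacological treatment will be used to compare the benefits of each intervention".

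The Measurements section defines the pharmacy-record version of adherence as doses removed over doses prescribed, as a percentage. It also says that "every time a patient buys their medication, the pharmacist registers the date of prescription, the date of dispensation and the number of pills dispensed", and that remaining stock is counted at 3 and 6 months.

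A second source on medicines is the adapted CSRI, described in the earlier Economic evaluation section under Measurements: "Patients are asked to give details of services and medicines that they have used during the previous 3 months". It covers use for depression and for other reasons.

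Nowhere does the costing rule refer to the recorded pill counts. It does not say whether the daily dose is the one prescribed or the one taken, or how days on treatment are counted.

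**The concern.** The programme aims to raise the share of prescribed doses that patients take, and the Sample size section is built on a 17-point difference in that share. If more doses are taken because more packs are bought, someone pays for them, and an ICER should carry that payment in its numerator. A rule that multiplies a regimen dose by days on treatment does not register purchases skipped during the treatment period. It would credit the intervention with the extra doses and not charge it for buying them.

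The cost-effectiveness result has consequences. It is one of the stated aims, and the Discussion says that proven effectiveness and cost-effectiveness would lead to a recommendation to adopt the programme in usual care. The arms otherwise differ by design mainly in pharmacist time, expected to be 20 to 30 minutes at the first contact and 10 to 15 minutes later. A modest drug-cost difference could therefore be visible beside the programme's own cost.

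**Working it through.** The article states no drug cost and no ICER, so there is no figure of its own to reproduce here. The total of 194 patients does not enter this point.

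**Inputs**
- Target difference: 17 points in percentage of medication intake (Sample size).
- Follow-up: 6 months, taken as 180 days (my convention).
- Cost rule and adherence definition: as described above. The economic section does not name the adherence measure; I use the pharmacy-record percentage.
- Assumptions: the daily dose is the prescribed dose, doses prescribed run over the full 180 days in both arms, and no part-used pack is left over when a patient stops.
- Drug price: not given. I assume EUR 0.30 to 1.50 per day to show the range.

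**Step 1: two patients.** Both have the same dose and 180 days on treatment. One removes 70% of doses and the other 87% (illustrative levels, 17 points apart). Let C be the cost of a full six-month course.
- Formula: C for each, difference 0.
- If the missed doses were never bought: 0.87C − 0.70C = 0.17C, which the formula misses.
- If both collected every pack and left pills unused: C for each, difference 0, and the formula is right.

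**Step 2: general form.** Let s be the share of the 17-point gap that comes from earlier stopping. Let u be the share of the remaining missed doses that were never bought.
- Extra daily doses taken per patient: 0.17 × 180 = 30.6.
- Counted by the formula, through days on treatment: 30.6 × s.
- Bought but not counted: 30.6 × (1 − s) × u.

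| Share from earlier stopping (s) | Counted by formula | Not counted, u = 1 | Not counted, u = 0.5 | Not counted, u = 0 |
|---|---|---|---|---|
| 0% | 0 | 30.6 | 15.3 | 0 |
| 25% | 7.65 | 22.95 | 11.475 | 0 |
| 50% | 15.3 | 15.3 | 7.65 | 0 |
| 75% | 22.95 | 7.65 | 3.825 | 0 |
| 100% | 30.6 | 0 | 0 | 0 |

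(All in daily doses per patient.)

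**Step 3: the limits.** The most that can be missed is 30.6/180 = 17% of a full course, that is 0.17C. Per point of adherence gained this is 0.17C/17 = 0.01C, or 30.6/17 = 1.8 daily doses. At the assumed prices the maximum is 30.6 × 0.30 = EUR 9.18 to 30.6 × 1.50 = EUR 45.90 per patient. The least is 0. The article gives neither s nor u.

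**The case against.** The strongest answer is that the wording does not fix the reading on which the concern depends. The daily dose could be the dose taken, and days on treatment could be days of supply obtained. The CSRI asks about medicines used, which points that way. On such a reading drug cost does move with adherence. A condensed article may also leave these definitions to the full protocol. That stands in part: the omission is conditional. But the costing formula itself is stated in the article and contains no quantity dispensed. Read naturally, a daily dose in milligrams is the regimen dose.

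The second answer is that unused pills in a bought pack have been paid for. Stock is counted precisely because dispensed and removed doses differ. If both arms collect all packs, costing by quantity dispensed gives the same zero increment as the formula. That stands in full, and it makes 0.17C an upper bound.

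The third is that one rule for all medicines is defensible, because pill counts exist only for antidepressants, and that the amounts are small. The first part is a real cost of changing the rule. The second is plausible, but the article gives no price from which to judge it.

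A reader might go further and infer that drug cost does not respond to adherence at all, so that the ICER is biased towards the intervention by 17% of a course. The document does not support this. Days on treatment capture longer persistence, bought but unused pills are a genuine cost, and the two key terms are undefined.

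**Conclusion.** The point holds in a limited form. With the daily dose read as the prescribed dose, the rule does not register doses never purchased while the patient remains on treatment, although the ICER's effect does. Incremental antidepressant cost is then understated only to the extent that better adherence means more packs bought during treatment. At the 17-point target that is between 0 and at most 17% of a full six-month course.

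The upper limit needs three things together: equal time on treatment in both arms, a gap made up wholly of missed doses, and none of those doses bought. For doses missed and not bought, and if adherence does improve, the direction favours the intervention. The net direction and size cannot be settled from the document. Part-used packs left when control patients stop early, for instance, would pull the other way.

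The primary adherence comparison is unaffected. What is at issue is whether cost and effect in the ICER rest on the same record, which matters for a stated aim of the trial.

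**What to change.** Cost study antidepressants as the quantity dispensed in the pharmacy record, multiplied by the price including VAT. Keep the milligram formula for other medicines reported through the CSRI. Report the milligram formula for antidepressants as a sensitivity analysis, and state for it whether the daily dose is prescribed or taken and how days on treatment are counted.

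No new data are needed, because the number of pills is registered at every dispensation. The change puts two costing bases into one total, which should be said openly, and the ICER may come out slightly less favourable to the programme. Antidepressants must also be removed from the CSRI medicine costs so that they are not counted twice.
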